## Abstract

**Background:**

Obstructive sleep apnea is a common sleep disorder in stroke patients. Obstructive sleep apnea is associated with stroke severity and poor functional outcome. Continuous positive airway pressure seems to improve functional recovery in stroke rehabilitation. To date, the effect of continuous positive airway pressure on cognitive functioning in stroke patients is not well established. The current study will investigate the effectiveness of continuous positive airway pressure on both cognitive and functional outcomes in stroke patients with obstructive sleep apnea.

**Methods/Design:**

A randomized controlled trial will be conducted on the neurorehabilitation unit of Heliomare, a rehabilitation center in the Netherlands. Seventy stroke patients with obstructive sleep apnea will be randomly allocated to an intervention or control group (n = 2×35). The intervention will consist of four weeks of continuous positive airway pressure treatment. Patients allocated to the control group will receive four weeks of treatment as usual. Outcomes will be assessed at baseline, immediately after the intervention and at two-month follow-up.

In a supplementary study, these 70 patients with obstructive sleep apnea will be compared to 70 stroke patients without obstructive sleep apnea with respect to cognitive and functional status at rehabilitation admission. Additionally, the societal participation of both groups will be assessed at six months and one year after inclusion.

**Discussion:**

This study will provide novel information on the effects of obstructive sleep apnea and its treatment with continuous positive airway pressure on rehabilitation outcomes after stroke.

**Trial registration:**

Trial registration number: Dutch Trial Register NTR3412

## Background

Obstructive sleep apnea (OSA) is a sleep disorder characterized by repetitive cessations of breathing during sleep due to obstruction of the upper airway. The diagnosis of OSA is based on the mean number of apneas and hypopneas per hour sleep, the apnea-hypopnea index (AHI). Nighttime consequences of OSA are periodic oxygen desaturations, increases in blood pressure and sleep fragmentation. OSA is associated with an increased risk for cardiovascular diseases, such as hypertension, heart disease and stroke [1,2]. A recent meta-analysis [3] reported a prevalence of sleep apnea between 38-72% in stroke patients compared to 3-28% in the general population [4].

The most frequently reported daytime consequences of OSA are excessive daytime sleepiness and fatigue. There is also growing evidence that OSA negatively affects cognitive functioning and mood. Most studies find impairment in the cognitive domains of vigilance, attention, executive functioning, memory and motor coordination [5,6]. The etiology of the cognitive impairment in OSA patients is still unclear, but neuroimaging studies provide evidence that OSA is associated with structural and functional changes in the brain, particularly in the frontal cortex and hippocampus [7,8].

Continuous positive airway pressure (CPAP) is the treatment of choice for OSA. CPAP improves breathing during sleep, resulting in better blood oxygen saturation and less sleep fragmentation [9]. Consequently, it is expected that CPAP treatment will improve daytime functioning. However, evidence of the therapeutic effects of CPAP on fatigue, cognitive functioning and mood is inconsistent. A Cochrane review showed significant reduction of objective and subjective sleepiness, and depressive symptoms, while in a recent meta-analysis of cognitive functioning after CPAP we only found slight improvement in the attention domain [10,11]. Notwithstanding this limited evidence for behavioral effects of CPAP treatment, there are some indications that it results in structural changes in the brain. One imaging study showed that CPAP treatment was associated with increase of grey matter in the hippocampal and frontal structures [8].

OSA is a common sleep disorder in stroke and has been reported to be associated with stroke severity, poor functional outcome, recurrent stroke, and increased mortality [2,12-14]. In a cross-sectional study in stroke patients, OSA was found to be associated with delirium, depressed mood and impaired activities of daily living, but no relationship was seen between OSA and performance on a cognitive screening instrument (Mini Mental State Examination; MMSE) [15]. The authors suggested the use of more sensitive neuropsychological tests. We conducted a pilot study examining the effect of OSA on a set of neuropsychological tests in stroke patients [16]. In this small sample, OSA was found to be associated with lower performance on tasks of attention, verbal memory and visual scanning, and increased depressive symptoms.

To date, seven randomized controlled trials (RCTs) have compared CPAP to treatment as usual (TAU) or sham CPAP in stroke patients. Four of these studies found improvement in CPAP compared to TAU in one or more neurological function outcomes, sleepiness or mood [15,17-19], while three RCTs found no benefit of CPAP treatment in these areas compared to TAU or sham CPAP [20-22]. The latter studies had low compliance and insufficient power due to small sample size, which may have affected the results. The effect of CPAP on cognitive functioning was evaluated in three studies. Two studies used the MMSE [15,21] and one study [19] assessed the sustained attention to response test (a measure of vigilance) and the digit or spatial span backward test (a measure of executive function). None of these cognitive measures showed improvement with CPAP. The effect on more extensive neuropsychological assessment including sensitive measures of memory and attention has not yet been investigated.

In summary, previous research suggests that OSA is associated with poor functional outcome after stroke, and that treatment with CPAP improves functional recovery during stroke rehabilitation. However, the effect of OSA and CPAP treatment on cognitive functioning in stroke patients is still unclear. The Treatment of OSA and Rehabilitation Outcome in Stroke (TOROS) study is designed to address these issues.

The TOROS project consists of a randomized controlled trial (RCT), and a supplementary case–control study. The primary objective of the RCT is to evaluate whether CPAP treatment improves cognitive and functional outcomes in stroke patients with OSA (AHI ≥ 15), as assessed by a neuropsychological test battery and by measures of neurological status and functional dependence. The aim of the supplementary case–control study is to explore the association between OSA and cognitive and functional status in stroke patients. Our hypothesis is that stroke patients with OSA have a poorer functional status and greater cognitive impairment compared to stroke patients without OSA. In both the RCT and the case–control study the secondary objectives are: 1) to evaluate the effects of OSA (and its treatment) on sleep quality, fatigue and mood; and 2) to evaluate the long-term effects of OSA on societal participation.

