## Methods

### Design

In the RCT, 70 OSA patients will be randomized to receive four weeks of CPAP treatment or four weeks of TAU. Patients randomized to TAU will start with CPAP treatment after the four-week intervention period. Neuropsychological assessment and examination of functional status, the primary outcome measures, are conducted at baseline and repeated after the four-week intervention period and at two-month follow-up. The secondary measures sleep quality, fatigue, and mood are assessed at the same time points as the primary outcome measures. To ascertain whether OSA improves with CPAP treatment, direct measurements of OSA, including AHI and level of oxygen desaturation during sleep, are made at baseline, at the end of the intervention period, and at two-month follow-up. To assess treatment compliance, the CPAP device registers CPAP usage per night, the air pressure and the residual AHI. At four weeks, and three, six and twelve months after enrollment the rehabilitation physician checks the compliance.

To test the hypothesis of the case–control study that OSA is associated with poor functional status and greater cognitive impairment, 70 stroke patients diagnosed with OSA are compared to 70 stroke patients without OSA on the primary and secondary outcomes at admission to the rehabilitation unit (baseline).

In a subgroup of the stroke patients without OSA (N = 35) the assessment of primary and secondary outcome measures will be repeated after four weeks and three months. The outcomes will be compared to the recovery of OSA patients.

All patients included in the TOROS study are asked to fill out a questionnaire on participation in work, leisure and social activities at six months and one year after inclusion. The study design is illustrated in Figure 1.

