### Secondary outcomes

Secondary outcome measures of the TOROS study are sleepiness (Stanford Sleepiness Scale), fatigue (Checklist Individual Strength), mood (Hospital Anxiety and Depression Scale), and subjective sleep quality (Sleep Quality Scale) [31-34]. A trained psychological assistant administers these measures after the neuropsychological assessment. The Utrecht Scale for Evaluation of Rehabilitation – Participation [35] is used to evaluate work, leisure and social activities at six months and one year after the inclusion. The patients complete this questionnaire at home.

Objective measurements of sleep are made using standardized pulse oximetry (WristOx®; Nonin Medical, Plymouth, USA) and ambulatory overnight cardiorespiratory polygraphy (Embletta®; Embla, Ottowa, Canada). The ODI (mean number of oxygen desaturations of ≥3% per hour) is calculated from the pulse oximetry data using automated analysis. Trained staff manually scores the polygraph recordings. Apnea is defined as a reduction of airflow of ≥90% for at least 10 seconds and hypopnea is defined as a reduction of airflow of ≥50% for at least 10 seconds followed by an oxygen desaturation of ≥3%. The AHI is defined as the mean number of apneas and hypopneas per hour in bed. The change of AHI measured by polygraphy and treatment compliance are used as moderating variables in the RCT.

A self-report questionnaire is administered to identify OSA symptoms (e.g., snoring, daytime sleepiness, morning headaches). Socio-demographic and clinical characteristics such as age, sex, education, body mass index (BMI), medication use and life style variables (e.g., smoking) are obtained from medical records.

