### Statistical analyses

All statistical analyses will be performed with SPSS 19 (IBM; Armonck, USA) or later versions of this package. Depending on the level of measurement, parametric statistics (Student’s *t*-test and analysis of (co)variance) or non-parametric statistics (*χ*^2^ and Fisher’s exact test) will be used. Statistical significance will be set at a p-value of 0.05 or less. Socio-demographic and clinical characteristics at baseline will be presented using descriptive statistics. If group differences are observed at baseline on one or more background variables, those variables will be included as covariates in all further analyses.

For the RCT, the therapy effects on the primary and secondary outcome measures will be examined using a two factor (group × time) multivariate analysis of variance (MANOVA). Effect sizes will be calculated for all analyses using standard statistical procedures. To control for the multiple comparisons of cognition and functional status, two separate MANOVA’s will be performed. Given that we have two primary outcomes defined for the study (i.e., cognitive and functional outcomes), we will subsequently follow Hochberg’s step-up procedure [36] to control the false discovery rate.

Data will be analyzed according to the intention-to-treat principle. Additionally, a per-protocol analysis will be performed. Depending on the variability of compliance, a secondary analysis of good versus poor compliance will be conducted. In an exploratory analysis, we will investigate whether the effectiveness of CPAP therapy varies as a function of clinical diagnosis, level of cognitive functioning, and demographic background.

For the supplementary case–control part of the study, OSA patients will be compared with the control group of non-OSA patients on primary and secondary outcome measures using a MANOVA. As with the RCT, a separate analysis will be performed for cognition and functional status, and the Hochberg’s step-up procedure will be followed. For the follow-up of the USER-P questionnaire, within group changes will be assessed using paired t-tests and between group comparison will be made with two sample *t*-test.

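### The long-term objective is worded as an effect of OSA, but participation is measured only after both trial arms have been assigned CPAP, and the USER-P t-test conflicts with the plan's own covariate rule

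*Protocol article*

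**What the plan says.** All references are to the protocol article.

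- **Objective (Background, last paragraph).** For both the RCT and the case–control study, the second secondary objective is "2) to evaluate the long-term effects of OSA on societal participation". The first secondary objective mentions treatment alongside OSA; the second does not. The aim of the case–control study itself is put more cautiously: "to explore the association between OSA and cognitive and functional status in stroke patients".
- **Treatment after week four (Design).** "Patients randomized to TAU will start with CPAP treatment after the four-week intervention period". CPAP use is followed for a year: "At four weeks, and three, six and twelve months after enrollment the rehabilitation physician checks the compliance".
- **Timing and groups.** Under Secondary outcomes, the USER-P "is used to evaluate work, leisure and social activities at six months and one year after the inclusion". The abstract says that "the societal participation of both groups will be assessed at six months and one year after inclusion", and that the OSA side of the supplementary study consists of the 70 trial patients.
- **Analysis (Statistical analyses).** "For the follow-up of the USER-P questionnaire, within group changes will be assessed using paired t-tests", and the between-group comparison is a two-sample t-test. Earlier in the section a general rule makes background variables that differ between groups at baseline covariates in all later analyses.
- **Recovery comparison (Design).** Thirty-five non-OSA patients are reassessed at four weeks and three months. "The outcomes will be compared to the recovery of OSA patients". Neither the arm nor the test is named.

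**The concern.** An objective about the effect of OSA needs OSA patients whose disease is left alone, or at least a defined contrast in exposure. At six and twelve months the design has neither. The treatment is also meant to remove the exposure: under Intervention, pressure is adjusted until the ODI is below 5, the same oximetry cut-off that classes a patient as non-OSA under Patient sample and procedures.

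Two misreadings follow. A null result could be reported as OSA having no lasting effect on participation when CPAP may have worked. A difference could be reported as an effect of OSA when the groups were formed by ODI and AHI and may differ in age, BMI or other characteristics. The plan has a rule against the second problem, but the test it names for USER-P has no place for covariates.

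**Working it through.** **1. Who is untreated, and when**

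| Time | CPAP arm (35) | TAU arm (35) | Non-OSA |
|---|---|---|---|
| Baseline | before trial CPAP | before trial CPAP | no OSA (70) |
| 4 weeks | assigned CPAP | not yet on CPAP | no OSA (35 reassessed) |
| 3 months | assigned CPAP | assigned CPAP | no OSA (35 reassessed) |
| 6 and 12 months (USER-P) | assigned CPAP | assigned CPAP | no OSA (70) |

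Continuation to twelve months is inferred from the compliance checks. An untreated OSA versus non-OSA contrast exists at baseline and, through the TAU arm, at four weeks. None exists at the USER-P visits.

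**2. The plan's own case–control figure**

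Inputs (Sample size): 70 per group, 0.5 SD, 90% power. The significance level is printed as 0.5. With the normal approximation, power = Φ(d·√(n/2) − z), and d·√(n/2) = 0.5 × √35 = 2.958.

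- One-sided 0.05: Φ(2.958 − 1.645) = 90.5%; required n = 69 per group. This reproduces the stated figure.
- Two-sided 0.05: Φ(2.958 − 1.960) = 84.1%; required n = 85 per group.
- Level 0.5 as printed: 98.9% two-sided, 99.8% one-sided.

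The stated figure is reproduced only if the level is read as one-sided 0.05. That is a separate matter; both sidednesses are shown below. The 0.5 SD was set for the case–control sample, not specifically for USER-P, and is borrowed here.

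**3. Dilution at six and twelve months (illustration; the share removed is assumed)**

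Apparent difference = 0.5 × (1 − share of the OSA effect removed by CPAP), at 70 v 70.

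| Share removed | Apparent difference | Power, two-sided 0.05 | Power, one-sided 0.05 |
|---|---|---|---|
| 0% | 0.500 SD | 84% | 91% |
| 25% | 0.375 SD | 60% | 72% |
| 50% | 0.250 SD | 32% | 43% |
| 67% | 0.165 SD | 16% | 25% |

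The last row takes the compliance expected under Sample size (about 67%) and assumes that compliers lose the whole deficit.

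**4. Unadjusted comparison (illustration; the shift is assumed)**

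Suppose OSA has no effect but the groups differ by a confounding shift b. The standard error is √(2/70) = 0.169 SD, and the rejection rate of a two-sided 5% test is Φ(b/0.169 − 1.960) + Φ(−b/0.169 − 1.960). For b = 0.1, 0.2 and 0.3 SD this gives 9%, 22% and 43%.

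**5. Untreated contrast at week four**

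TAU (35) versus non-OSA (35) at 0.5 SD: 0.5 × √17.5 = 2.092, and Φ(2.092 − 1.960) = 55% two-sided. If all 70 OSA patients were used instead, the multiplier is √(70 × 35/105) = 4.830. With nothing removed, power is Φ(2.415 − 1.960) = 68%. If CPAP removed the effect in 67% of the CPAP half, the difference is 0.5 × (1 − 0.5 × 0.67) = 0.3325 SD and power is Φ(1.606 − 1.960) = 36%.

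**The case against.** The strongest reply is that this is a secondary objective in a study whose supplementary part sets out only to explore an association. The case–control hypothesis is tested at baseline, before any trial CPAP, and the randomised comparison at four weeks is untouched. That stands, and it limits the weight of the point. It does not repair the objective, which uses the language of effects for visits at which every trial OSA patient has been assigned treatment.

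Several stronger readings are tempting, but the documents do not support them:

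- **That the recovery comparison contains no untreated OSA patients, or pools the arms.** The TAU arm is not on CPAP up to week four. Pooling is not stated, and a non-OSA subgroup of 35 matches the size of one arm. The fair criticism is only that the article does not say which OSA patients are meant.
- **That recovery is analysed by t-test.** The t-test is stated only for USER-P. OSA and non-OSA patients are compared on primary and secondary outcomes by MANOVA, and no test is named for recovery.
- **That nothing is adjusted for.** The covariate rule exists and would reach characteristics such as age and BMI. The problem is that it and the two-sample t-test cannot both be followed.
- **That the paired test is invalid.** It validly tests change from six to twelve months. No baseline USER-P is mentioned, so it does not show change since inclusion.
- **That power is 16%.** This is one end of an assumed range. It carries a compliance figure justified by the short experimental phase out to a year and assumes full benefit in compliers, although the Background calls the evidence for CPAP's daytime benefits inconsistent.

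**Conclusion.** The point holds as a mismatch between a secondary objective and what is measured, together with a conflict within Statistical analyses. At six and twelve months the available contrasts are OSA patients offered CPAP versus patients without OSA, and immediate versus four-week-delayed CPAP. Neither is the long-term effect of untreated OSA.

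This conclusion rests on the stated design. Its numerical size does not: on the assumptions shown, two-sided power for a true 0.5 SD lies between 84% and 16%, depending on how much of the deficit CPAP removes. Being on CPAP means being assigned it; actual use at a year is unknown.

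A reader might infer that the trial can say nothing about untreated OSA. That goes too far: the baseline comparison and the TAU arm at week four both allow it, as non-randomised associations. The change should be made because it alters what the participation results can be said to show.

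**What to change.** 1. **Reword the objective:** participation at six and twelve months in OSA patients offered CPAP versus patients without OSA, reported as an association. Describe any comparison of the randomised arms at these visits as immediate versus delayed CPAP.
2. **Replace the between-group USER-P t-test** with ANCOVA or regression on a prespecified list of background covariates already collected, for example age, sex, education and BMI. Adjust for baseline neurological status and dependence only as a sensitivity analysis: the trial hypothesises that OSA worsens functional status, so adjusting for these could remove part of the association sought. The paired test can stay, labelled as change from six to twelve months.
3. **Name the OSA group in the recovery comparison:** TAU arm (35) versus non-OSA (35) at four weeks as the untreated contrast, and label the three-month comparison as OSA assigned to CPAP.

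The cost is wording and one model, with no new data. The week-four contrast uses 35 OSA patients and has about 55% two-sided power for 0.5 SD. Using all 70 would give between 68% and 36% under the assumptions above, so restricting to TAU does not necessarily lose power.

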## Methods

### Design

In the RCT, 70 OSA patients will be randomized to receive four weeks of CPAP treatment or four weeks of TAU. Patients randomized to TAU will start with CPAP treatment after the four-week intervention period. Neuropsychological assessment and examination of functional status, the primary outcome measures, are conducted at baseline and repeated after the four-week intervention period and at two-month follow-up. The secondary measures sleep quality, fatigue, and mood are assessed at the same time points as the primary outcome measures. To ascertain whether OSA improves with CPAP treatment, direct measurements of OSA, including AHI and level of oxygen desaturation during sleep, are made at baseline, at the end of the intervention period, and at two-month follow-up. To assess treatment compliance, the CPAP device registers CPAP usage per night, the air pressure and the residual AHI. At four weeks, and three, six and twelve months after enrollment the rehabilitation physician checks the compliance.

To test the hypothesis of the case–control study that OSA is associated with poor functional status and greater cognitive impairment, 70 stroke patients diagnosed with OSA are compared to 70 stroke patients without OSA on the primary and secondary outcomes at admission to the rehabilitation unit (baseline).

In a subgroup of the stroke patients without OSA (N = 35) the assessment of primary and secondary outcome measures will be repeated after four weeks and three months. The outcomes will be compared to the recovery of OSA patients.

All patients included in the TOROS study are asked to fill out a questionnaire on participation in work, leisure and social activities at six months and one year after inclusion. The study design is illustrated in Figure 1.

